### 3.6. Step 6. Evaluation Plan

According to the program goal, which was set based on the need’s assessment in step 1, the hypotheses will test whether the mental health status and perceived family functioning improved in the intervention group relative to the comparison group. The primary outcome will be the effect of the program on mental health issues including depression, internalizing and externalizing behaviors, psychological distress, and suicidality among adolescents. These indicators were determined based on a review regarding outcome variables used in previous experimental studies of runaway and homeless adolescents. The secondary outcome will be the effect of the program on perceived family functioning among adolescents. The process evaluation should address the reach (percentage of the intended participants who used the program) and the dose of the intervention (average dose received by program participants). We will evaluate whether the needs of participants, as assessed in step 1, will be satisfied, and the new information and perspective generated in the evaluation process of the program will help us revise the previous steps in the IM process.

The effectiveness of the developed program will be evaluated in a randomized controlled trial (RCT). The participants will be divided into experimental and comparison groups via computer-generated random allocation. The participants that meet the following criteria will be included: runaway adolescents residing in youth shelters and 12–18 years of age. The exclusion criteria will be as follows: (1) adolescents diagnosed with an intellectual disability or specific learning disorder that can impair their ability to understand the intervention procedure and (2) those who are currently receiving other psychiatric treatments. In addition, family members currently receiving treatment for acute psychiatric symptoms will not be allowed to participate in the family sessions.

The participants’ data will be collected using self-administered questionnaire surveys, which will be completed individually in quiet counseling rooms to protect the participants’ confidentiality. The assessment time points will include the baseline (before the program) and immediately and 1 month after program completion.

The data will be analyzed statistically using IBM SPSS Statistics for Windows, version 26.0 (IBM Corp., Armonk, NY, USA), and the intervention effects will be examined using a one-way repeated measure multivariate analysis of variance (MANOVA). A power analysis conducted using the G * Power program [36] indicated that a total sample of 211 subjects would be needed to detect a medium effect (*f* = 0.25) with 80% power using MANOVA at an alpha level of 0.05. Therefore, we will collect data from 118 participants each in the experimental and comparison groups (*N* = 236) to accommodate the expected attrition of 10% over the three-month period from the baseline assessment to the final evaluation.

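### Read naturally, the repeated-measures MANOVA makes baseline an outcome occasion; this is valid, but using baseline as a covariate would give more power from the same data

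*Protocol article*

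**What the plan says.** All of this stands in the Protocol article, section 3.6 (Step 6, Evaluation Plan).

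- Visits: "The assessment time points will include the baseline (before the program) and immediately and 1 month after program completion".
- Hypothesis: "the hypotheses will test whether the mental health status and perceived family functioning improved in the intervention group relative to the comparison group".
- Primary outcome: "mental health issues including depression, internalizing and externalizing behaviors, psychological distress, and suicidality among adolescents". Counting internalizing and externalizing behaviors separately, this is five variables.
- Method: "the intervention effects will be examined using a one-way repeated measure multivariate analysis of variance (MANOVA". No covariate or other baseline adjustment is mentioned anywhere in the article.
- Sample size: "a total sample of 211 subjects would be needed". The target behind that number is 80% power for f = 0.25 with MANOVA and alpha 0.05. Recruitment is then set at 118 per group, 236 in all, for 10% attrition.

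The article does not state which occasions form the response vector. A repeated-measures analysis over three listed visits, serving a hypothesis about relative improvement, most naturally takes all three and reads the effect from the group-by-time term.

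**The concern.** Randomisation makes the expected baseline difference zero. An analysis with baseline as an outcome does not use that knowledge. Its group-by-time test compares changes from baseline, which amounts to fixing the coefficient of the baseline score at 1. Conditioning on baseline lets the data set that coefficient, which in large samples is at least as precise and also corrects chance imbalance between groups.

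What is at stake is power and precision. The primary test spreads over five scales and two post-program visits (10 numerator degrees of freedom), so lost noncentrality can matter. The baseline scores are collected in any case.

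**Working it through.** **Inputs.** From section 3.6: N = 211 evaluable, two equal groups, f = 0.25 (f² = 0.0625), alpha 0.05, p = 5 primary outcomes, three visits. Assumed, because the article gives no figure: equal correlation rho between any two visits, the same for all five scales; no group difference at baseline; f = 0.25 as the multivariate effect at a post-program visit.

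**1. The plan's own figure.** For a two-group MANOVA of five outcomes at one occasion:

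- lambda = N·f² = 211 × 0.0625 = 13.19, with df = 5 and 211 − 5 − 1 = 205.
- Power is 0.8003, so 211 is reproduced exactly. With attrition, 211/0.9 = 234.4, hence 235, and 236 for equal groups.

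The stated N therefore draws on neither the repeated visits nor the baseline. A repeated-measures within-between calculation with three occasions would give 158.

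**2. Baseline as an outcome occasion (group-by-time, 10 and 200 df).** The multiplier on N·f² is 2/(3(1 − rho)), both when the effect is the same at the two post-program visits and when it is gone by 1 month. If it halves by 1 month, the multiplier is 0.5/(1 − rho).

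**3. Baseline as covariate (both post-program visits jointly, 10 and 195 df).** The denominator is 211 − 2 − 5 − 10 + 1 = 195, because five covariates are fitted. With D = (1 − rho)(1 + 2rho), the multipliers are:

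- sustained effect: 2/D
- halved by 1 month: (1.25 + 0.25·rho)/D
- gone by 1 month: (1 + rho)/D

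For a sustained effect at rho = 0.3, lambda is 13.19 × 2/2.1 = 12.56 for group-by-time and 13.19 × 2/(0.7 × 1.6) = 23.55 with adjustment. The ratio is 3/(1 + 2rho): 1.88, 1.50 and 1.25 at rho 0.3, 0.5 and 0.7.

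**4. Power at N = 211 (group-by-time → baseline-adjusted, both with 10 numerator df).**

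| rho | Sustained | Halved by 1 month | Gone by 1 month |
|---|---|---|---|
| 0.3 | 0.64 → 0.93 | 0.49 → 0.76 | 0.64 → 0.75 |
| 0.4 | 0.72 → 0.94 | 0.57 → 0.78 | 0.72 → 0.80 |
| 0.5 | 0.82 → 0.96 | 0.67 → 0.83 | 0.82 → 0.87 |
| 0.6 | 0.91 → 0.98 | 0.785 → 0.89 | 0.91 → 0.93 |
| 0.7 | 0.975 → 0.994 | 0.91 → 0.955 | 0.975 → 0.983 |

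For a sustained effect, the N needed for 80% power is 283 against 156 at rho 0.3, 205 against 140 at 0.5, and 127 against 104 at 0.7. The adjusted figures are slightly favourable, since chance baseline imbalance costs a little beyond the five degrees of freedom.

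**5. Averaging the two post-program visits (5 df, baseline-adjusted).** Power is 0.975, 0.987 and 0.999 at rho 0.3, 0.5 and 0.7 if the effect is sustained, but 0.41, 0.46 and 0.62 if it is gone by 1 month.

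**6. Other readings of the named method.** If the test were the group main effect averaged over all three occasions, baseline would dilute it: power 0.71, 0.60 and 0.51 at rho 0.3, 0.5 and 0.7. If baseline were left out and one post-program visit analysed (5 df), power would be 0.80; adding baseline as covariate gives 0.84, 0.91 and 0.985.

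**The case against.** The strongest reply is that nothing here is an error. The sentence on visits only lists them, and the MANOVA sentence does not say which occasions enter or which contrast is tested. Group-by-time is a valid test of relative improvement, and a condensed article may leave covariates to a fuller plan. Part of this stands: the role of baseline is inferred, and the point is about efficiency, not validity. It does not remove the point, because the article names a specific method without a covariate, and on each reading computed adjusting for baseline does better.

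Some stronger readings are tempting but unsupported:

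- *Setting the 10-df group-by-time test against a 5-df adjusted test at a single visit.* At rho 0.5 both have multiplier 1.33, so the whole gap from 82% to 91% comes from dropping five degrees of freedom. Only the matched 10-df comparison isolates the role of baseline.
- *Inferring that the trial misses 80% power as planned.* With the full effect at both post-program visits, group-by-time reaches 0.82 at rho 0.5 and 0.975 at 0.7.
- *Taking the 97–99% power of the post-program mean at rho 0.3 to 0.5 as what the trial gives up.* That requires an effect that lasts to 1 month.
- *Concluding that no stratification is planned.* The article mentions only computer-generated random allocation, and silence in a condensed text is not a plan.

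**Conclusion.** The point holds as an avoidable loss of efficiency in the analysis as named. It is not a bias, and it is not an error in the stated sample size.

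The loss is substantial at visit correlations of about 0.3 to 0.5 when the effect lasts, and small at 0.7 or above. It is also smaller if the effect has gone by 1 month. With the full effect at both post-program visits, group-by-time falls below the stated 80% only at rho 0.3 and 0.4 among the values computed (0.3 to 0.8). If the effect halves by 1 month, it is also below at 0.5 and 0.6. Adjustment does not guarantee 80% in every case: at rho 0.3 it reaches 0.75 if the effect is gone by 1 month.

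These sizes rest on the assumed correlation structure and on reading baseline as one of the repeated occasions.

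**What to change.** Keep the three visits. State that the two post-program visits are the outcomes, analysed jointly, with the baseline score of each scale as covariate. This can be a MANCOVA or a mixed model with a separate group effect at each post-program visit. Apply the same rule to perceived family functioning. Do not rest the primary test on the mean of the two post-program visits alone, because it loses most of its power if the effect fades.

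The cost is small: five denominator degrees of freedom for the covariates in the primary MANCOVA, and a rewritten power sentence that matches the chosen test and gives the assumed visit correlation. No further participants or visits are needed. The Conclusions place the trial in the future, so the change can be made before it starts.

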## 4. Discussion

In this article, we have described the systematic development process of a family-based mental health program for runaway adolescents residing in youth shelters. Although previous studies conducted theory- and evidence-based psychological interventions for this population [15,17], to our knowledge, only a few studies conducted tailored interventions that considered their family context among runaway adolescents in Korea. The strengths of the IM protocol used in this study include the application of a structured and systematic development process, the development of a tailored program that considers the socio-cultural context and stakeholders, and an emphasis on theory- and evidence-based intervention [19]. Therefore, we used the IM protocol to develop a tailored theory- and evidence-based program for runaway adolescents in Korea, despite it being a time- and effort-consuming process.

The first strength of our developed program involves its basis on a comprehensive needs assessment, which combined a literature review and the results of interviews with runaway adolescents and youth shelter workers. From an ecological perspective, the needs assessment identified the individual and family factors influencing the mental health problems of runaway adolescents. We also identified the youth shelters where runaway adolescents reside as appropriate settings in which to implement the intervention. These findings led to the design of our program to incorporate individual sessions and family sessions within a shelter setting.

The second strength of our developed program is its emphasis on a theoretical framework in combination with the need’s assessment. In this study, the transactional model of stress and coping [30] and the Walsh family resilience framework [31] provided the rationales for the behavioral outcome- and interpersonal environmental outcome-related performance objectives. We also used theory- and evidence-informed decisions to select effective change methods. We expect that this approach will help to close the gaps among the scientific evidence, practice, and policy in the field of community mental health.

Our study differs from prior studies because we identified psychiatric and mental health nurses at community mental health centers linked to youth shelters as the program implementers. A systematic review study identified that the program implementers in previous intervention studies of homeless and runaway adolescents were research investigators, such as counselors, nurses, psychologists, and clinicians [37]. When considering how to enable the adoption, implementation, and maintenance of the program, however, we considered that youth shelters refer adolescents with mental health issues to community mental health centers, where the cases are managed by the nurses. By considering the system linking youth shelters and community mental health centers, this program implementation plan will help to maintain the program itself, as well as the initial adoption and implementation.

The IM protocol provided a useful framework in developing a program to target runaway adolescents in this study, suggesting the application of the IM protocol in the field of mental health promotion. For this program, we adopted an individual approach, which enabled customization to the individual needs and circumstances of runaway adolescents, and a family intervention modality, which was intended to intervene in family problems because these were identified as the main cause underlying runaway behavior. The effectiveness of the developed program on mental health status and perceived family functioning of runaway adolescents remains to be demonstrated in further RCTs.

### Limitations

This study had several limitations. First, although we used a comprehensive needs assessment including reviewing literature and theories, focus group interviews, and individual interviews, limited numbers of participants were interviewed because of recruiting only participants from the participating shelters involving in our development process. Second, although this study implemented the IM protocol to consider environmental and individual factors via an ecological approach, the developed program did not combine environmental components beyond the family level. Other environmental factors such as school and society factors may have important effects on the mental health and quality of life of runaway adolescents. Therefore, further studies with a more comprehensive approach that incorporates school and societal efforts are needed. Third, this study set the overall change objectives in consideration of the runaway and family contexts of the target population. However, it may be necessary to set detailed change objectives according to the mental health status and family conflict level experienced by each adolescent.

## 5. Conclusions

The IM protocol-based program development in this study yielded a theory- and evidence-based intervention that was tailored specifically to the needs of runaway adolescents residing in youth shelters. The program incorporated both individual and family sessions developed in consideration of the runaway and family contexts. In addition, this program will be provided by psychiatric and mental health nurses at community mental health centers linked to youth shelters. In the future, an RCT will be conducted to evaluate the effects of this program based on our evaluation plan.

## Figures and Tables

**Table 1 ijerph-17-07794-t001:** Matrix of behavioral and environmental outcomes.

Outcomes	Performance Objectives	Determinants			
		Attitudes	Knowledge	Skills	Self-Efficacy
Behavioral Outcome: Adolescents Adapt to Stressful Situations	PO.1. Adolescents use effective coping strategies for stress.	A.1. Adolescents express a more positive perspective of stressful situations.	K.1. Adolescents list effective coping strategies.	SK.1. Adolescents demonstrate and apply effective coping strategies.	SE.1. Adolescents express confidence in using effective coping strategies.
	PO.2. Adolescents seek help from social support networks in stressful situations.	A.2. Adolescents express positive attitudes toward seeking help.	K.2.a. Adolescents list available helping resources. K.2.b. Adolescents identify benefits of seeking help from formal resources.	SK.2. Adolescents demonstrate help-seeking behavior in stressful and risky situations.	SE.2. Adolescents express confidence in help-seeking behavior.
Environmental outcome: Families Become More Resourceful in Dealing with Family Adversities	PO.3. Family members rebuild family relationships.	A.3.a. Family members recognize meanings of family adversities. A.3.b. Family members express positive attitudes toward reconciliation of wounded relationships.	K.3.a. Family members identify individual needs and differences K.3.b. Family members identify ways to express mutual empathy and support.	SK.3. Family members demonstrate mutual empathy and support.	SE.3. Family members express confidence in reconciliation of wounded relationships through mutual empathy and support.
	PO.4. Family members communicate clearly and honestly.	A.4. Family members express positive feelings about family communication.	K.4. Family members identify ways to communicate clearly and honestly with other family members.	SK.4. Family members demonstrate ability to communicate clearly and honestly.	SE.4. Family members express confidence in ability to communicate clearly and honestly.
	PO.5. Family members collaborate to solve family problems.	A.5.a. Family members recognize family strength. A.5.b. Family members express proactive stance for collaborative problem solving and decision making.	K.5. Family members identify ways of collaborative problem solving and decision making.	SK.5. Family members demonstrate collaborative problem-solving and decision-making skills.	SE.5. Family members express confidence in collaborative problem solving and decision making.

**Table 2 ijerph-17-07794-t002:** Changeable determinants, theory- and evidence-based change methods, and practical applications.

Determinants	Methods	Practical Applications
Attitude	Motivational interviewing	Strengthen personal motivation for and commitment to positive changes
	Cognitive reappraisal	Use cognitive reappraisal to reframe one’s thoughts in a more positive perspective
Knowledge	Consciousness-raising	Provide information and feedback
Skills	Skills training	Develop skills from activity-based learning
	Guided practice	Role-play in multiple scenarios
Self-efficacy	Social modeling	Mentor–mentee activities
	Improving emotional states	Relaxation training
	Verbal persuasion	Provide strong encouragement

**Table 3 ijerph-17-07794-t003:** Scope and sequence of a family-based mental health program for adolescents residing in youth shelters.

Intervention Modality	Session	Contents	Methods, Practical Applications, Activities
Individual Adolescent Session	1	Engagement and establishing motivation for program	Establishing the therapeutic alliance Establishing motivation for change
	2	Positive thinking: A (Antecedent events), B (Beliefs or thoughts), and C (Consequences)	Identifying stressful events, automatic thoughts, and responses (emotions or behaviors) Modifying negative thoughts to more positive thoughts Practice positive self-talk
	3	Coping with stressful situations	Providing information and feedback about coping strategies Coping skills training Relaxation training
	4	Asking for help to handle stressful situations	Providing information about stressful and risky situations and helping resources Role-play in multiple scenarios Mentor–mentee activities Providing strong encouragement and support
Family Session	5	Family engagement and establishing motivation for change	Family engagement activities Establishing the therapeutic alliance Establishing motivation for change
	6	Rebuilding relationships with family	Positive reframing of family adversities Providing information and feedback about adolescents’ developmental needs and parental needs Empathy skills training Practice interacting positively with each other
	7	Improving family communication	Communication skills training Family role-play Providing strong encouragement
	8	Improving collaborative problem solving	Highlight family strengths Skills training in collaborative problem solving and decision making Family meetings
